## Abstract

**Background:**

Current guidelines for opioid dependence recommend daily maintenance of physical dependence with methadone or buprenorphine, and discourage abstinence due to the high risk of relapse and overdose. Extended-release formulations of the opioid antagonist naltrexone (XR-NTX) block heroin and other opioid agonists competitively for around 4 weeks per administration. XR-NTX thus enables opioid users to experience abstinence from opioid agonists with greatly reduced risk of overdose compared to medication-free abstinence. While XR-NTX has shown promise compared to placebo and daily naltrexone tablets, there is limited information on long-term safety and its performance compared to daily maintenance treatment.

**Methods/Design:**

In this five-hospital RCT with long-term follow-up, we aim to recruit *n* = 180 patients in treatment for opioid dependence and allocate them in an open, randomized manner (1:1) to receive either 4-week XR-NTX or daily buprenorphine-naloxone (BP-NLX) for the duration of 12 weeks. Allocation is open-label due to the risk of overdose during attempts to self-unmask allocation using heroin. Urine drug tests are scheduled every week with follow-up visits & assessment every 4 weeks. Primary outcomes are abstinence from illicit opioids in urine drug tests and self-report, as well as retention in treatment. Secondary outcomes include other substance use, injecting behavior, drug craving, mental health, quality of life, treatment satisfaction, abstinence motivation, opioid agonist effect rating, insomnia, and pain. Observation is continued for another 36 weeks in order to assess longer-term safety, adherence and effectiveness. The study is an investigator-initiated trial, funded by public grants and approved by an Independent Ethical Committee (the Regional Ethical Committee for Research South-East B # 2011/1320) and the Norwegian Medicines Agency.

**Discussion:**

Despite minor implementation problems, the protocol appears sufficiently robust to generate results of high interest to patients, clinicians and policy makers.

**Trial registration:**

Clinicaltrials.gov # NCT01717963, first registered: Oct 28, 2012. Protocol version # 3C, June 12th 2012.

## Background

Death from opioid overdose is the leading cause of death among drug users, and has more than doubled in the US over the last 15 years [1, 2] in what is often characterized as an ‘overdose epidemic.’ A main mechanism is the development of addiction to opioid agonist drugs like heroin and/or illicit diversion of prescribed opioid medications [3]. A chronically relapsing disorder [4], addiction to illicit opioids often includes criminal activity, poly-drug use and blood-borne infections such as HIV [5].

Due to high risk of relapse and overdose associated with abstinence, the preferred treatment for opioid addiction is substitution of the illicit opioid with a prescribed opioid medication like the full opioid agonist methadone [6] or partial opioid agonist buprenorphine [5]. This agonist replacement therapy (ART) is generally effective at reducing illicit opioid use, overdose mortality [7], as well as important drug-related outcomes such as criminal activity [8] and injection-related disease [9].

As ART presents a risk of illicit diversion and abuse of prescribed methadone or buprenorphine [10], ART providers will often attempt to minimize this risk by utilizing control measures such as supervised medication intake, urine drug screens, limits on take-home dosing and–travel outside the catchment area [5, 11]. A disadvantage of these control measures is their tendency to reduce patients’ sense of personal freedom, potentially undermining their motivation to remain in ART [5]. As methadone, a full opioid agonist, is considered to have a high potential for abuse and overdose, the partial opioid agonist buprenorphine is sometimes preferred. The abuse risk of buprenorphine can be further reduced when combined with a component of the short-acting opioid antagonist naloxone; this combination product tends to not cause withdrawal when ingested correctly (sublingually), but is likely to cause some withdrawal symptoms if the medication is injected [12].

Despite the dilemmas inherent in treating opioid users with opioid agonists, current guidelines recommend ART due to its ability to retain patients in treatment while greatly reducing illicit opioid use and overdose risk [5]. This in contrast to the other main treatment principle, medication-free abstinence, which is generally not recommended due to the elevated risk of overdose following a period of abstinence from opioid agonists. Despite the risks, treatment based on medication-free abstinence is available in most countries, e.g. as long-term residential treatment or therapeutic communities with outpatient follow-up.

A main concern for opioid addiction treatment is its limited uptake in the user population: Only about 50 % of the patient base are estimated to be in treatment at any one time [5, 13]. The potential human and social benefit of increasing the number of opioid users in treatment is the main incentive to exploring novel treatment approaches.

One recent innovation is sustained release formulations of the opioid antagonist naltrexone [14–16] (SRX). Following detoxification from all opioid agonists (e.g. heroin, morphine, methadone, buprenorphine), naltrexone medication will support the person in avoiding relapse by rendering attempts at relapse futile: as naltrexone competitively blocks the action of heroin and other opioid agonists, the drug euphoria (or ‘high’) as well as sedative effects should effectively be inaccessible to the patient. The only version of SRX currently approved by the FDA, extended release naltrexone (XR-NTX), is administered intramuscularly in the gluteus where it releases naltrexone at therapeutic levels for the duration of 4–5 weeks per injection. XR-NTX appears superior to placebo in both laboratory and clinical settings [17–19]; other sustained release naltrexone (SRX) formulations have shown promising results compared to daily oral naltrexone [20, 21] and to usual-treatment controls [22, 23].

Given the success of ART in clinical practice, a valid policy question is the need to implement another treatment like extended-release naltrexone for the target disorder, opioid dependence. This is best addressed by a randomized controlled trial of long-acting naltrexone with the currently most similar ART medication on offer, daily ART with buprenorphine-naloxone.

In addition to the advantages offered by a randomized comparison, most observers emphasize the need for observation beyond the 8 to 24 weeks often reserved for RCTs [3, 4, 24]. With XR-NTX, only a handful of studies have so far investigated long-term outcomes [25–27]. Long-term observation will also improve the accuracy estimates of occurrence of adverse events. Oral naltrexone tablets has been available since the 1980s, but lack of adherence undermines clinical efficacy [28] and creates uncertainty about the validity of safety data.

Although naltrexone has shown the ability to reduce craving for several substances of abuse e.g. alcohol [29, 30] and heroin [31], there is still clinical interest in whether poly-drug using patients will increase non-opioid substance use during XR-NTX. Other long-term consequences of opioid antagonism are also subject to debate, mainly based on preclinical and/or case data: Some suggest naltrexone could reverse receptor-level changes attributed to chronic opioid agonist intake [32]; others think it plausible naltrexone could increase users’ vulnerability to overdose upon discontinuation of the medication [33] due to chronic antagonism stimulating receptor growth and sensitivity.

The present protocol describes a study of adult opioid users randomized to receive either 4-week intramuscular naltrexone (XR-NTX) or daily buprenorphine-naloxone (BP-NLX) in a clinical setting. The purpose of the study is to explore recovery–and medication-related outcomes of similarly motivated patients randomized to either treatment. For ethical reasons, patients will not be discontinued from XR-NTX but permitted to receive XR-NTX for up to 48 Weeks total, providing an opportunity to observe longer-term effects of chronic medication with XR-NTX.

## Methods/Design

### Study design

This is a 12-week open-label randomized-controlled trial comparing 4-week intramuscular injections of extended release naltrexone (XR-NTX) to a currently recommended treatment for opioid addiction, daily buprenorphine-naloxone (BP-NLX). As this is he first RCT comparing these two medications, we consider the scientific approach to be exploratory.

For ethical reasons (see below) study medication (XR-NTX) will not be terminated upon RCT completion, but will be available for an additional 36 weeks (48 weeks total observation time). This will produce long-term data clinical safety and effectiveness of chronic naltrexone treatment. Registry data collection of mortality, morbidity, criminal justice and prescription records will take place before, during and after the prospective data observation in order to provide additional information on the volunteers and long-term effects of XR-NTX medication.

### Research questions and hypotheses

The main research question is whether 4-week XR-NTX will be more effective than–or equally effective to a current standard treatment–daily BP-NLX–on primary and secondary outcomes during or at the end of the 12-Week study.

As an exploratory study with both non-superiority and superiority as plausible scenarios [34] there are two sets of hypotheses for this RCT:

XR-NTX will influence primary and secondary outcomes to be either:statistically superior to assignment to the current standard treatment, ART with daily BP-NLX orstatistically non-superior to ART with daily BP-NLX.

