### Statistical analyses

Statistical analyses on the randomized part of the study will be conducted by a non-study statistician on a final RCT data set in which the two study medications is masked as ‘Rx A’ and ‘Rx B’; any obvious characteristics of the two comparison medications will also be censored before data are made available for analysis. For between- group comparisons and to control for the effect of baseline characteristics, we will use a General Linear Mixed Models (GLMM) approach containing factors for treatment group, sex, and sex-by- treatment interaction, and with age, duration of opioid dependence, and duration of last pre-study inpatient detoxification as covariates. For outcomes violating the normality assumption, a General Alinear Mixed Models (GAMM) approach will be used. Regular statistics (e.g. ANOVA, linear regression) may be utilized if the arguments for using GLMM or GAMM over legacy analysis types are considered to provide limited benefit. Retention will be assessed with Kaplan-Meier curves and a log-rank test. Adverse events will be compared using Fisher’s exact test. The primary endpoints are tested with a two-sided α = 0.05. Where relevant, *p* values will be adjusted for multiplicity using the Bonferroni-Holm method to preserve family-wise type 1 error at 0.05. Once the statistician concludes data analysis of the RCT phase, study management will be able to access the final dataset.

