#### Determination of sample size

In compliance with current recommendations for non-superiority trials [34], a minimum sample size has been estimated for two scenarios:

The superiority scenario assumes that XR-NTX participants will have opioid-negative samples on a mean of 7 out of the total 12 (7/12 or 0.58) samples, while participants receiving buprenorphine-naloxone will display a mean of 4 opioid-negative samples (4/12 or 0.33). With a 95 % significance level (*p* < 0.05) and a standard deviation of 3 in both medication groups, and power (beta) set to 90 %, a sample size of 17 patients/medication arm or *n* = 34 total is estimated to be sufficient for analysis. The estimated frequency of opioid use in each group is based on data from Norwegian patients receiving sustained release naltrexone [22] or on the frequency of illicit opioid use during buprenorphine maintenance in the Norwegian national ART program.

In the non-superiority scenario, using a beta of 90 %, we assume that both groups will retain 70 % of their participants at the end of Week 12 and set 20 % as the non-superiority margin; this yields a minimum sample size of *n* = 58 in each group/*n* = 116 total.

Based on the sample size calculations and the risk of dropout of a significant proportion of participants, we have set the recruitment target for *n* = 180 total, or *n* = 90 for each medication group. This will be facilitated by characteristics of design (few exclusion criteria, open-label allocation, outpatient data collection often coinciding with medication and counseling), prioritization of amount–and types of data collected. Information about the study will be distributed at clinical sites as well as outreach -, housing- and criminal justice facilities and the internet; these efforts are anticipated to attract the initial *n* = 30 patients whose presence in the larger community of opioid users will be sufficiently inform more potential participants to contact study staff for information.

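### The second hypothesis is worded as 'non-superior', which any worse XR-NTX result satisfies, and the 20-point retention margin is not carried into the analysis

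*Protocol article*

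**What the plan says.** All references are to the protocol article.

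- **Research questions and hypotheses.** The main question is whether XR-NTX is "more effective than–or equally effective to a current standard treatment–daily BP-NLX–on primary and secondary outcomes". Two hypotheses follow: XR-NTX is statistically superior, or it is statistically "non-superior to ART with daily BP-NLX".
- **Determination of sample size.** The same term recurs: "In compliance with current recommendations for non-superiority trials [34], a minimum sample size has been estimated for two scenarios". For the second scenario the article assumes that "both groups will retain 70 % of their participants at the end of Week 12" and says the authors "set 20 % as the non-superiority margin", with 90% power (labelled beta). It arrives at 58 per group; the recruitment target is 90 per group. The direction of the margin is not stated, and no margin is given for urine-test or self-reported abstinence.
- **Outcomes & instruments.** Retention is defined both as days in treatment (of at most 84) and as the number of patients completing at Week 12. The margin belongs to the second definition.
- **Statistical analyses.** "Retention will be assessed with Kaplan-Meier curves and a log-rank test". Other outcomes are compared with mixed models or conventional methods. Primary endpoints are tested at two-sided 0.05, with Bonferroni-Holm adjustment where relevant. The 20% margin does not appear here.

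**The concern.** The two hypotheses are complements. Every possible result makes XR-NTX either superior or not superior, so the pair cannot be refuted. A result in which XR-NTX is significantly worse falls under the second hypothesis, although the question it is meant to serve is whether XR-NTX is as good as standard treatment.

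The wording is also out of step with the sizing. Equal assumed retention in both arms with a 20-point margin is a non-inferiority or equivalence set-up under another name. The stated analysis is a set of difference tests. A log-rank test compares whole retention curves under a null of no difference; it does not set the Week-12 proportion against a margin.

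At stake is half of the main question: a claim of comparability with an established treatment. The plan as written has no test that could confirm or deny it.

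**Working it through.** **Inputs.** From the sample-size section: 70% retention in both arms, margin 0.20, power 90%, 58 per group (stated minimum), 90 per group (target). From the analysis section: two-sided 0.05. Assumed here: a non-inferiority level of one-sided 0.025, the counterpart of two-sided 0.05, since the article states no one-sided level; true XR-NTX retention of 70%, 60% or 50%; normal approximations throughout.

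**1. The plan's own figure.** For non-inferiority, n per arm = 2 × 0.70 × 0.30 × (z_α + z_power)² / 0.20² = 10.5 × (z_α + z_power)².
- One-sided 0.05: 10.5 × (1.645 + 1.282)² = 89.9, so 90.
- One-sided 0.025: 10.5 × (1.960 + 1.282)² = 110.3, so 111.

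The stated 58 is not reproduced. It is a separate matter and the present point does not depend on it. The 90 per arm target coincides with the one-sided 0.05 result.

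**2. How often 'non-superior' is met.** Read it as not significantly better at two-sided 0.05. With 90 per arm, d = p_X − 0.70 and SE = √[(0.21 + p_X(1 − p_X))/90], the probability is Φ(1.96 − d/SE). For comparison, a non-inferiority test with the 20-point margin at one-sided 0.025 passes with probability Φ((d + 0.20)/SE − 1.96).

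| True XR-NTX retention | SE | 'Non-superior' met | Non-inferiority shown |
|---|---|---|---|
| 70% | 0.0683 | 97.5% | 83.3% |
| 60% | 0.0707 | 99.96% | 29.3% |
| 50% | 0.0715 | about 100% | 2.5% |

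The worse XR-NTX is, the more surely the written hypothesis is met.

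**3. A single result.** Suppose 45/90 (XR-NTX) against 63/90 (BP-NLX) are retained. The difference is −0.20 and SE = √(0.25/90 + 0.21/90) = 0.0715. The 95% CI is −0.20 ± 1.96 × 0.0715, that is −34 to −6 points (p about 0.005). XR-NTX is significantly worse, and 'non-superior' is satisfied.

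**4. A different error: reading a non-significant test as equality.** For a two-sided 5% two-proportion test with pooled null variance, power = Φ[(|d| − 1.96 × SE₀)/SE₁], where SE₀ is the pooled and SE₁ the unpooled standard error.
- 70% v 50%, 90 per arm: (0.20 − 1.96 × 0.0730)/0.0715 = 0.795; power 78.7%, non-significant 21%.
- 70% v 50%, 58 per arm: (0.20 − 1.96 × 0.0910)/0.0891 = 0.244; power 59.6%, non-significant 40%.
- 70% v 60%, 90 per arm: (0.10 − 1.96 × 0.0711)/0.0707 = −0.557; power 28.9%, non-significant 71%.

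A non-inferiority test at one-sided 0.025 would pass 2.5% of the time at the margin.

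**5. Power of the repaired test.** With both arms at 70% and 90 analysed per arm, SE = √(0.42/90) = 0.0683 and 0.20/SE = 2.928. At one-sided 0.025, Φ(2.928 − 1.960) = 83.3%. At one-sided 0.05, Φ(2.928 − 1.645) = 90.0%.

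**The case against.** The best defence is that this is a mislabelled non-inferiority design. The equal assumed rates, the margin and the cited guidance all point that way, and Week-12 completion is a defined outcome. A confidence interval for the difference could be set against 20 points without new data. That stands. A reader might infer that the trial cannot support any comparability claim, and this goes too far: it is true of the stated analysis, not of the data for retention.

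A reader might also infer that the trial plans to treat a non-significant test as proof of equality. The article states no such rule. The 21%, 40% and 71% in step 4 show what would follow if someone read it that way; they do not measure the defect in the wording itself, which step 2 does.

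The study calls itself exploratory and presents the two hypotheses as plausible scenarios. That tempers how firmly any conclusion should be drawn, but primary endpoints are still tested at 0.05 with multiplicity control, and one of the two sample-size scenarios is based on this hypothesis.

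Finally, a fuller protocol or SAP may hold the confidence-limit rule, the one-sided level and the test order. Their absence from an article is no fault, and none is alleged. What remains is a hypothesis stated wrongly in two sections, and stated tests that do not match the stated margin.

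**Conclusion.** The point holds as an error in what is written. The second hypothesis is met by equality and by any degree of inferiority, so it does not address the research question. The only margin given covers one outcome, has no direction, and is not used by the stated analysis.

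Size: with 90 per arm and 70% BP-NLX retention, the hypothesis is met in 97.5% of trials under true equality and in about 100% when true XR-NTX retention is 50%, where a non-inferiority test would pass in 2.5%. These figures rest on the article's 70%, on 'non-superior' meaning not significantly better at two-sided 0.05, and on a one-sided 0.025 non-inferiority level, which is an assumption. That the margin was meant for non-inferiority is likely but not certain; equivalence would also fit the wording of the question.

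**What to change.** 1. In the hypotheses and sample-size sections, replace 'non-superior' and 'non-superiority' with 'non-inferior' and 'non-inferiority'. In the research question, replace the equal-effectiveness phrase with 'not worse than, by the stated margin', because a 20-point margin cannot show equality.
2. Add to the statistical analyses: 'Non-inferiority on Week-12 retention is concluded if the lower limit of the two-sided 95% confidence interval for the difference in completion (XR-NTX minus BP-NLX, all randomised patients) lies above −20 percentage points. Superiority is tested next.' Keep the log-rank test as supportive.
3. Do not also require the result in a per-protocol set. The example in the Analysis sets section admits only medication-compliant patients who attend all four follow-ups, so Week-12 completion there is near 100% in both arms by construction.
4. Limit the urine-test and self-reported abstinence outcomes to superiority with a 95% confidence interval. Recruitment is described as running to July 2015 and allocation is open to study staff, so a margin chosen now, with only the statistician's dataset masked, would carry little weight.
5. Restate the power.

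**Cost.** Wording and one confidence interval; no new data. Any equality claim on abstinence is given up. At one-sided 0.025 with the article's inputs, 90 analysed per arm gives 83% power, not 90%, and 111 per arm would be needed for 90%. The 90% holds with 90 per arm only at one-sided 0.05. These figures are before any Bonferroni-Holm adjustment, so the plan should say whether that applies to this test.

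### The second hypothesis and its 20% margin are worded as non-superiority where non-inferiority appears to be meant, so a clearly worse XR-NTX arm would satisfy the hypothesis as written

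*Protocol article*

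**What the plan says.** The section Research questions and hypotheses asks whether XR-NTX is "more effective than–or equally effective to a current standard treatment". The two hypotheses that follow are that XR-NTX will be "statistically superior to assignment to the current standard treatment" or that it will be statistically "non-superior to ART with daily BP-NLX". Both are applied to the primary and the secondary outcomes. The same section introduces them with "As an exploratory study with both non-superiority and superiority as plausible scenarios".

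Determination of sample size keeps the term. It assumes that "both groups will retain 70 % of their participants at the end of Week 12", has the plan "set 20 % as the non-superiority margin", aims for 90% power, and arrives at 58 per group. The superiority scenario is sized on a different endpoint, the number of opioid-negative urine tests. The recruitment target is 90 per group.

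Statistical analyses gives mixed models for between-group comparisons, Kaplan-Meier curves with a log-rank test for retention, and a two-sided 0.05 level for the primary endpoints. It mentions no margin and no confidence bound.

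**The concern.** Non-superior means not better, and that includes any degree of worse. The research question asks about equal effectiveness; neither hypothesis says it. A margin attached to non-superiority, taken literally, limits how much better XR-NTX may be, whereas the question needs a limit on how much worse.

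The wording is consistent, so it cannot be passed over as a single slip. The term occurs five times: twice in the hypotheses section and three times in the sample-size section. Non-inferior and non-inferiority occur nowhere in the article. The only analyses described are tests for a difference, so a reader who wants to know when the second hypothesis is met has only a non-significant superiority test to go on. At stake is whether a null or unfavourable retention result can be presented as support for a pre-stated hypothesis, and from there as equal effectiveness.

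**Working it through.** **Inputs.** From Determination of sample size: Week-12 retention 70% in both arms, margin 20% (read here as absolute percentage points), 90% power, 58 per group, target 90 per group. From Statistical analyses: two-sided 0.05, hence one-sided 0.025 for a bound. No separate alpha is given for the margin comparison, so 0.05 and 0.10 one-sided are shown as well.

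**The plan's own figure.** For non-inferiority of two proportions, n per arm = [2 × 0.7 × 0.3] × (z(1-α) + z(0.90))² / 0.20², that is 0.42 × (z(1-α) + 1.2816)² / 0.04.

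- α = 0.025: 110.3, so 111 per arm
- α = 0.05: 89.9, so 90 per arm
- α = 0.10: 68.98, so 69 per arm

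The stated 58 is not reproduced at any of these levels. That is a separate matter; the point about wording does not depend on it.

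**Power with the stated numbers.** SE = √(0.42/n), and power = Φ(0.20/SE - z(1-α)).

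- n = 58: SE = 0.0851, 0.20/SE = 2.350; power 65% (α = 0.025), 76% (0.05), 86% (0.10)
- n = 90: SE = 0.0683, 0.20/SE = 2.928; power 83% (0.025), 90% (0.05), 95% (0.10)

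**What each reading of the second hypothesis accepts.** Exact binomial enumeration of Week-12 retention, 90 per arm, BP-NLX at 70%, Wald 95% intervals for XR-NTX minus BP-NLX:

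| True XR-NTX retention | Not superior (lower bound not above 0) | Literal non-superiority margin (upper bound below +20 points) | Non-inferiority (lower bound above -20 points) |
|---|---|---|---|
| 70% | 97.4% | 83% | 83% |
| 60% | 99.96% | 98.9% | 29% |
| 50% | about 100% | 99.98% | 2.5% |
| 40% | about 100% | about 100% | 0.03% |

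Under both literal readings, the worse XR-NTX does, the more surely the second hypothesis is met. Under non-inferiority the order is reversed.

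**What the two-sided difference test would show.** At 50% versus 70%, SE = √((0.25 + 0.21)/90) = 0.0715, and the chance that XR-NTX is found significantly worse is Φ(0.20/0.0715 - 1.96) = about 80%.

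**The case against.** The strongest reply is that non-inferiority was obviously meant. The research question comes just before the hypotheses, and equal rates, a margin and a power target are the structure of a non-inferiority calculation. This is probably right as to intent, and it makes the correction easy. It does not cure the text: the reader still has to supply the word, the direction of the margin and the test.

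A reader might go further and infer that the two hypotheses cover every possible result, so that the trial cannot fail or cannot answer its own question. The document does not support that. Under the probable intent, the retention hypothesis can fail. If the margin is taken literally as an upper limit of +20 points, some results meet neither hypothesis (14% of trials at 90 per arm with 70% in both arms). The two-sided test would also expose a clearly worse arm in about 80% of trials at 50% versus 70%. Nor does the article state a rule that a failed superiority test is to be reported as equal effectiveness; the wording only leaves that reading open.

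The study calls itself exploratory, which lowers the weight of formal confirmation. It nevertheless names primary endpoints, fixes an alpha and sizes one scenario on this margin. An analysis plan that is not shown could define the test, but the point here is what the article states wrongly, not what it leaves out.

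**Conclusion.** The point holds for the hypotheses and margin as worded. The second hypothesis is framed in the wrong direction and is met almost always by an XR-NTX arm that is 20 points worse in Week-12 retention, where a non-inferiority rule would be met in about 2.5% of trials. The result for a much worse arm is the same whether non-superior means simply not superior or an upper bound below +20 points.

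The figures assume 70% retention on BP-NLX, an absolute margin, 90 analysed per arm and Wald intervals. The mismatch between question and hypothesis needs none of these assumptions. Because the wording governs what the trial may claim, it should be corrected before the treatment codes are opened.

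**What to change.** - In Research questions and hypotheses and in Determination of sample size, replace the term with non-inferiority. State that for Week-12 retention the lower confidence bound of XR-NTX minus BP-NLX must lie above -20 percentage points, and name the one-sided alpha.
- Add that comparison to Statistical analyses, and to the analysis plan if there is one.
- Restrict the non-inferiority claim to Week-12 retention, the only outcome with a margin. Keep superiority testing for the other outcomes. No order between non-inferiority and superiority need be imposed, since the plan sizes them on different endpoints.
- State that a non-significant superiority test does not show equal effectiveness, and that a lower bound at or below -20 points is reported as non-inferiority not shown.
- Restate the power. With 70% in both arms and a two-sided 95% interval it is about 65% at 58 per arm and 83% at 90; the stated 90% needs 111 per arm. A one-sided 0.05 would give 90% at 90 per arm, but it is a weaker standard than the two-sided 0.05 stated for the primary endpoints and would have to be declared.

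The cost is wording and a less favourable stated power. No new data are needed. The trial may then end with non-inferiority not shown.
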